What is the impact of SUSTAIN on GPs? (eg, confidence and skills in pediatric care and use of clinical guidelines)	GP web-based survey	Web-based control and intervention surveys completed by GPs via REDCap^d^.	Control surveys are collected in the month prior to the implementation commencing in each practice. Intervention surveys are collected in the last month of the implementation at each practice.	Changes in the level of confidence in pediatric care, level of knowledge and skill in navigating the health system for children, and reported use of clinical guidelines.
What is the impact of SUSTAIN on patients and family experience?	Family web-based survey	Web-based control and intervention surveys completed by families/caregivers via REDCap.	Control surveys are collected in the month prior to the implementation commencing in each practice. Intervention surveys are collected in the last month of the implementation at each practice.	Level of confidence in GP care, level of satisfaction with GP care, desire for referral to specialist care, and preference for GP or specialist review.
Health economic evaluation				
What is the cost of implementing the model of care? What is the cost- effectiveness?	Trial data and supplementary unit costings	Trial data on the model of care, health service activity, and combined with relevant unit costs.	Data will be collected throughout the model of care.	Costs of conducting the model of care compared with usual care and costs/cost offsets from changes in OP/ED referrals, MBS,^e^ and PBS^f^ (including out-of-pocket fees) compared with accessing usual care.
Implementation evaluation				

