**Figure 1. F1:**

Stepped wedge randomized control trial design.

Each general practice provides control period data (referral and medical record data) during the control period (standard GP care, no SUSTAIN model operating). Each month thereafter, 3 practices switch concurrently from control to intervention where a pediatrician supports GPs through telehealth coconsultations, virtual case-based discussions, and being available by phone and email contact in working hours. During the first month of the intervention for each practice, a 1-month transition period is allowed to embed the SUSTAIN model of care into the practice, where data do not contribute to the analysis. This embedding period assists with implementation of the model of care into the practice and allows time to address any procedural issues. After the embedding period, each practice is exposed to an 11-month intervention period. Sustainability data are collected following cessation of the intervention until the intervention is completed for the final practice.

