### Intervention

SUSTAIN is a 12-month-long virtual model of care offered to all consenting GPs in participating general practices. It consists of four components: (1) virtual GP-led, shared GP-pediatrician consulting sessions with patients younger than 18 years, (2) virtual pediatrician-led case discussion sessions, (3) phone/email pediatrician support, and (4) complimentary access to the internationally renowned SCHP learning platform (Figure 2).

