### Statistical Analysis

We will undertake descriptive analysis to describe the GP referral rate alongside the numbers of all children seen and the numbers of children referred to OP or ED by month during the study period for each practice.

All available data from each recruited GP and family will be analyzed according to an intention-to-treat principle. For the outcomes of GP referrals identified using the GP EMR data (eg, GP referral to OP clinic or ED), we will conduct mixed effects logistic regression, fitted to data collected during the control and intervention periods. The model will include a fixed effect of group (intervention vs control) and adjust for calendar time (as a continuous variable), and random effects to allow for variation in the outcomes for 3 hierarchical levels, including GP practice, GP within each practice, and patients seen by each GP.

Secondary outcomes collected at the child consultation level will be analyzed similarly, with separate models for the 5 common childhood conditions to measure quality of care. GP survey outcomes will be analyzed using mixed effects logistic regression, again including a fixed effect for group by intervention status and calendar time, and a random effect for GP practice, GPs, and patients.

We will control for baseline levels of GP referral for each practice in the analyses, GP-level factors (eg, rurality of the practice’s location, billing type, GP gender, years of practice, and number of children patients seen per week), and patient-level sociodemographic factors (eg, age at the encounter and socioeconomic status of residence). We will also consider whether the intervention effect varies by rurality of practice and GP-level factors (eg, referring level during baseline, years of practice, and GP gender) by the inclusion of interaction terms between group (intervention vs control) and these variables in the regression models.

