## Results

The trial is supported through a 2.5-year NSW Ministry of Health Translational Research Grants Scheme (TRGS Round 6). This includes direct funding for research staff, as well as in-kind contributions from the SCHN supporting 1.0 FTE pediatrician, estimated to be the appropriate allocation of pediatrician time for the number of practices from our previous experience with the SC4C study. GPs also receive complimentary enrollment in the SCHP, a pediatric web-based modular learning course for GPs. In-kind contributions from PHNs, Central Eastern Sydney Primary Health Network, South Western Sydney Primary Health Network, and South Eastern NSW Primary Health Network also contributed to support recruitment and ongoing engagement with general practices in each PHN region. From March 2023, general practice and GP recruitment commenced across GP practices in metropolitan and nonmetropolitan (regional, rural, and remote) areas in NSW. Data collection then started in all consented practices from September 1, 2023, with anticipated completion by February 28, 2025. The delivery of the virtual 12-month-long pediatric-integrated GP intervention commenced in the first practices from October 2023 and will conclude in the final practices at the end of February 2025. GP and practice staff are engaged in focus group discussions as part of the implementation evaluation midway through the intervention phase. Data analysis, report, and manuscript preparation will begin from March 2025, with results expected to be available by the first quarter of 2026.

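### The calendar-time term in the GP survey model is nearly collinear with intervention status, because each practice's two surveys are 12 months apart with no concurrent controls

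*Protocol article*

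**What the plan says.** Statistical Analysis sets the model for the survey outcomes: "GP survey outcomes will be analyzed using mixed effects logistic regression, again including a fixed effect for group by intervention status and calendar time", with "a random effect for GP practice, GPs, and patients". The word "again" points back to the referral model, which is to "adjust for calendar time (as a continuous variable", so I read time as one linear term in both.

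Table 1, under Objectives, sets the survey timing: "Control surveys are collected in the month prior to the implementation commencing in each practice", and "Intervention surveys are collected in the last month of the implementation at each practice". The Intervention section gives the length: "SUSTAIN is a 12-month-long virtual model of care offered to all consenting GPs in participating general practices". The text with Figure 1 gives the roll-out: "Each month thereafter, 3 practices switch concurrently from control to intervention". Sample Size Calculation gives 18 practices. Results adds: "Data collection then started in all consented practices from September 1, 2023", with first starts in October 2023 and the last practices finishing at the end of February 2025.

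**The concern.** In a stepped wedge, adjustment for time works because some practices are still in control while others are already in intervention in the same month. The referral data have this overlap, since they are extracted continuously. The surveys are taken only twice per practice, once just before the start and once in the final month, and the survey model seems to have been carried over from the referral model without allowing for this.

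If no month holds both control and intervention surveys, the data can hardly separate the effect of the model of care from a year of general change. GP confidence and skills are a named secondary objective. Followed as written, the model would give an interval too wide to interpret. If the term were dropped only after that had been seen, the choice of analysis would look data-driven.

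**Working it through.** **No survey figure to reproduce.** The article gives no power or precision for the GP survey. Its 90% power for referrals comes out at 91.2% with the same six-step layout (18 months, embedding month left out, month indicators, variance at the mean rate), so the layout is a fair reading of the design.

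**Schedule.** 18 practices at 3 per month make 6 steps. Count September 2023 as month 0.

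| Step | Control survey | Start | Intervention survey | Gap (months) |
|---|---|---|---|---|
| 1 | Sep 2023 (0) | Oct 2023 | Sep 2024 (12) | 12 |
| 2 | Oct 2023 (1) | Nov 2023 | Oct 2024 (13) | 12 |
| 3 | Nov 2023 (2) | Dec 2023 | Nov 2024 (14) | 12 |
| 4 | Dec 2023 (3) | Jan 2024 | Dec 2024 (15) | 12 |
| 5 | Jan 2024 (4) | Feb 2024 | Jan 2025 (16) | 12 |
| 6 | Feb 2024 (5) | Mar 2024 | Feb 2025 (17) | 12 |

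The last row agrees with the stated end in February 2025. Control surveys occupy months 0 to 5 and intervention surveys months 12 to 17, with no overlap.

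**Collinearity, from the schedule alone.**
- Variance of time within a survey round (six equally spaced months): 35/12 = 2.917.
- Variance between rounds (12 months apart, equal numbers): 6² = 36.
- r² = 36/38.917 = 0.925, so r = 0.962.
- Variance inflation factor = 1/(1 − 0.925) = 38.917/2.917 = 13.3.
- Standard error multiplier for independent responses: √13.34 = 3.65.

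**Is the model estimable?** With an intercept, intervention status and linear time, the design matrix has rank 3 of 3, so yes. With practice fixed effects the rank is 19 of 20, and with month indicators 12 of 13. Exact aliasing arises only in those two forms, or within a single practice.

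**Precision (linear approximation).** Let m be the GPs per practice, ρ the practice ICC, and g the extra correlation between two answers from the same GP. In units of the outcome's variance:

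- Without time: V₀ = 2(1 − ρ − g)/(18m).
- With linear time: V₁ = V₀ + (12²/52.5) × [ρ + g/m + (1 − ρ − g)/(2m)], where 52.5 = 18 × 35/12 is the sum of squares of start month across practices.

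The added term is the variance of the between-practice slope, multiplied up over 12 months. For an item near 50% the SD is 0.5, so the half-width is 1.96 × 0.5 × √V.

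Example with m = 5, ρ = 0.06, g = 0:
- V₀ = 1.88/90 = 0.0209. SE = 0.5 × 0.1445 = 0.072.
- V₁ = 0.0209 + 2.743 × 0.154 = 0.443. SE = 0.5 × 0.666 = 0.333.

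| m | ρ | g | Half-width without time (points) | With time (points) | Ratio |
|---|---|---|---|---|---|
| 10 | 0 | 0 | 10.3 | 37.7 | 3.65 |
| 5 | 0 | 0 | 14.6 | 53.4 | 3.65 |
| 10 | 0.06 | 0 | 10.0 | 54.0 | 5.4 |
| 5 | 0.06 | 0 | 14.2 | 65.2 | 4.6 |
| 10 | 0.06 | 0.7 | 5.1 | 61.4 | 12.1 |
| 5 | 0.06 | 0.7 | 7.2 | 77.1 | 10.8 |

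**Would more respondents help?** As m grows, V₁ tends to 144ρ/52.5. At ρ = 0.06 that is 12 × √(0.06/52.5) = 0.41 SD, a half-width of about 40 points. At ρ = 0.02 it is about 23 points.

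**The case against.** A reader might infer that intervention and time are perfectly confounded and the effect cannot be estimated. The article does not support that. It plans continuous time and random practice effects, under which the model is full rank. Because the start order is randomised, the between-practice slope is a legitimate estimate of trend if the trend is linear. The result would be imprecise, not meaningless. This stands, and it is why the point is near-collinearity. What remains is that linearity across the gap between the two survey rounds cannot be checked from these data.

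The interval widths rest on inputs that the article does not give. The ICC of 0.06 belongs to the referral outcome, and neither the number of GPs nor any within-GP correlation is stated. Half-widths above 50 points around a 50% item reflect the linear approximation, whereas the planned model is logistic. This also stands. Only r, the variance inflation factor and the 3.65 multiplier (for independent responses) follow from the schedule alone.

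A reader might extend the criticism to the family surveys. Their timing is similar, but the article states no calendar-time term for them. Nor does it claim a concurrent randomised comparison for the surveys. It calls them baseline and follow-up, and Limitations admits that the design is susceptible to calendar trends.

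Finally, removing the time term trades variance for possible bias from secular change. That is a fair reason to keep the adjusted model as a sensitivity analysis. It is not a reason to make it the main one.

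**Conclusion.** The concern holds for the GP survey in this form: the stated model is estimable but carries almost no information about the intervention. By the schedule, r is 0.96, the variance inflation factor 13.3, and the standard error at least 3.65 times that of the model without time. Under the assumed 5 to 10 GPs per practice, item near 50%, practice ICC 0 to 0.06 and within-GP correlation 0 to 0.7, the half-width is about 38 to 77 points with time and about 5 to 15 without. The 12-month gap is by scheduled month, and single responses may stray by some weeks.

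This should be fixed, but it concerns a secondary outcome with no stated power. The primary referral analysis has months in which control and intervention practices run side by side, and is unaffected.

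**What to change.** In Statistical Analysis, make the main GP survey analysis the change from the pre-intervention survey to the final-month survey, without the calendar-time term. Label it an uncontrolled before-after comparison, outside the randomised stepped-wedge evidence. The linear-time model may be kept as a sensitivity analysis, with its dependence on linear extrapolation stated.

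Pair responses by GP and use a practice random effect only if responses can be linked. GP and Family Data Collection says that GP name and practice are not attached to responses. The Data Management Plan gives every participant an ID code, which may or may not allow linkage. These statements need to be reconciled with the practice and GP random effects already planned.

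Give the family survey results the same before-after label. There is no stated time term to delete there.

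The cost is a change of wording, plus settling the linkage question, and a more modest claim. The main analysis loses its adjustment for secular change, which this survey schedule cannot credibly supply. Both surveys of a practice fall in the same calendar month one year apart, so a stable seasonal pattern cancels in the before-after change.

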### Data Collection

#### GP EMR Data Collection

To measure the primary outcome (ie, referrals to hospitals), pediatric referral data will be routinely collected from the GP EMRs via GRHANITE. This software will be remotely embedded into all participating GP medical software computers (compatible with BP or MD EMR software). For research purposes, GP data will be collected on all patients younger than 18 years. These data will be deidentified at the patient level, although the identity of the GP will be supplied to the research team. Collection of GP EMR referral data will commence for all practices following randomization and will continue for the duration of the trial.

The ability to record referral information, manage deidentification and consent processes, is a principal rationale for the use of the GRHANITE technologies and was demonstrated to be acceptable to GPs in the SC4C study [19].

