### Sample Size Calculation

In the SC4C pilot study, there was a 7% reduction in GP referrals to hospital EDs and OPs, but we have powered our trial using a conservative 4% reduction [19,32]. The sample size of 18 practices with at least 60 pediatric consultations per practice per month will have 90% power to detect a 3.7% reduction (from the baseline rate of 10%) in the percentage of children who are referred to OP clinics or EDs following their GP appointment, assuming an intracluster correlation of 0.06 (derived from the pilot data [19]) and 2-sided type I error of 0.05. With the same sample size, we will have 80% power to detect a 5.5%‐6.55% reduction in the proportion of referrals to OP or ED for our planned stratification analysis by practice rurality, GP baseline referring level, years of practice, and gender.

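### The primary model adjusts for a practice baseline referral level that can only be built from control outcomes already in the model: redundant with the practice random intercept, and mildly anti-conservative if taken over the whole control period

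*Protocol article*

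**What the plan says.** The Statistical Analysis section specifies a "mixed effects logistic regression, fitted to data collected during the control and intervention periods". It has a fixed effect of group, calendar time as a continuous variable, and random effects for practice, GP within practice, and patient within GP. The primary correlation structure is exchangeable within practice. The same section then says: "We will control for baseline levels of GP referral for each practice in the analyses". It does not say which months are baseline, or that those months leave the outcome data.

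On where a baseline could come from, GP EMR Data Collection says: "Collection of GP EMR referral data will commence for all practices following randomization". The GP Referrals section explains that the ordinary record does not hold referrals in usable form, which is why a purpose-built pop-up was developed. Textbox 1 and the Recruitment section ask each GP for at least two weeks of referral data, and place those weeks in the control period.

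The only stated error rate is in the Sample Size Calculation section: "2-sided type I error of 0.05".

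**The concern.** No referral data exist from before the control period. A practice's baseline level is therefore an average of outcomes that also sit on the left-hand side of the primary model.

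Write a practice's control-period average as its true level plus sampling error. When that average is entered as a covariate with a coefficient near one, it absorbs the true level, which is the random intercept's job. It also absorbs the sampling error of the same control outcomes it is then used to predict. Control residuals in each practice are pulled towards zero by construction, the estimated practice variance shrinks, and the model gives between-practice comparisons more weight and less uncertainty than they deserve.

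At stake is the calibration of the confidence interval and p-value for the primary comparison. Nothing is gained in return, because the random intercept already uses the control data to locate each practice.

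**Working it through.** **Inputs from the protocol.** "The sample size of 18 practices with at least 60 pediatric consultations per practice per month will have 90% power", for a fall from 10% to 6.3%, "assuming an intracluster correlation of 0.06". "Each month thereafter, 3 practices switch concurrently from control to intervention", so 18/3 = 6 steps. One embedding month is dropped and 11 intervention months follow. Data run from September 2023 to February 2025, 18 months, so control periods last 1 to 6 months according to step.

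**Step 1: reproduce the stated power.** Stepped-wedge generalised least squares on practice-month means, categorical months, exchangeable correlation.
- Mean rate p = (0.10 + 0.063)/2 = 0.0815, so p(1-p) = 0.07486.
- Practice variance = 0.06 x 0.07486 = 0.00449. Practice-month sampling variance = 0.94 x 0.07486/60 = 0.00117.
- On the layout above, SE of the effect = 0.01116.
- Power = Phi(0.037/0.01116 - 1.960) = Phi(1.354) = 91.2%, against the stated 90%.

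The layout therefore reproduces the plan's figure.

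**Step 2: null simulation on that layout.** Logistic model with a normal practice intercept (mean -2.438, SD 0.804 on the logit scale, which gives about 10% and an ICC of 0.06), no true effect and no secular trend. The fitted model has group, linear calendar time and a practice random intercept, by adaptive quadrature. The test rejects when |estimate/SE| > 1.96. There were 6,000 trials and no failed fits. The covariate is the logit of the practice's baseline referral rate.

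| Baseline covariate | Mean SE | True SD of estimate | Ratio | Rejection (Monte Carlo SE) | Median practice SD |
|---|---|---|---|---|---|
| None | 0.1062 | 0.1051 | 1.010 | 4.9% (0.28) | 0.764 |
| All control months | 0.1031 | 0.1079 | 0.955 | 6.3% (0.31) | 0.195 |
| Month 1 only | 0.1052 | 0.1064 | 0.988 | 5.3% (0.29) | 0.360 |

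The paired increase over no covariate is 1.4 points (SE 0.22) for all control months and 0.4 points (SE 0.14) for month 1. Bias is negligible (mean log odds ratio -0.002 with the all-control covariate). As a plausibility check, an SE ratio of 0.955 implies rejection of 2 x Phi(-1.96 x 0.955) = 6.1%, in line with the simulated 6.3%.

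With the all-control covariate the reported SE falls by 3% while the true SD rises by 3%. The estimate is slightly noisier and is reported as more precise.

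**Step 3: cross-checks, practice random intercept only, all-control covariate.**
- Gaussian REML, 24,000 trials: 5.3% without, 6.6% with (5.8% with month 1 only).
- A second Gaussian REML check: 5.7% without, 7.2% with; SE ratio 0.98 and 0.93.
- A separate logistic simulation with beta-distributed practice rates: 4.9% without, 6.7% with; SE 0.103 against a true SD of 0.111, 7% too small. Entering the rate on the raw scale made the SE 2-6% too small.
- One shorter logistic run (3,000 trials) did not show the direction in its rejection rates: 7.1% without, 6.2% with. It lost 132 of the unadjusted fits, so I give it no weight. Its SE ratios still ran the same way (0.973 without, 0.947 with).

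**Step 4: add the GP level that the protocol specifies.** Gaussian REML, 60,000 trials per scenario, residual variance taken as known, all-control covariate. The protocol gives neither the number of GPs per practice nor the GP share of the variance, so the rows show an assumed range.

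| ICC practice / GP | GPs per practice | With | Without |
|---|---|---|---|
| 0.05 / 0.01 | 5 | 6.2% | 5.0% |
| 0.045 / 0.015 | 5 | 6.0% | 5.0% |
| 0.03 / 0.03 | 5 | 5.5% | 5.0% |
| 0.03 / 0.03 | 3 | 5.5% | 5.2% |
| 0.06 / 0.03 | 5 | 5.6% | 5.0% |
| 0.02 / 0.04 | 5 | 5.3% | 5.0% |
| 0.06 / 0.06 | 5 | 5.1% | 5.0% |

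The excess is about 0.2 to 1.2 points and shrinks as GP variation grows. These are differences of rounded rates, so the last row, which reads 0.1, is compatible with 0.2.

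**The case against.** The strongest case against has three parts.

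First, the larger figures come from a model with practice effects only, whereas the protocol also specifies GP and patient random effects. Differences between GPs in the same practice keep the GP variance estimable, and that puts a floor under the variance of practice means. This stands: Step 4 shows the excess shrinking, in some scenarios almost to nothing.

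Second, baseline is not defined. September 2023 is a control month for every practice. If that month alone is used, the logistic rejection rate of 5.3% cannot be told apart from 5%. This stands too, and such a definition may sit in an analysis plan that is not shown. What the article does state is the adjustment itself, and on either definition the covariate is made of modelled outcomes.

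Third, misspecified correlation matters far more. With an assumed cluster autocorrelation of 0.8, the exchangeable model rejected 12.7% without and 13.4% with the covariate. That is a separate issue, for which the protocol already plans a block-exchangeable sensitivity analysis. It does not make this covariate useful.

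A reader might infer that the primary standard error is necessarily too small and that the type I error exceeds 5% whatever is done. The documents do not support that: it depends on the undefined baseline period and on a GP variance that they do not give. A reader might also object that the practice variance from this model is uninterpretable, but no section plans to interpret it.

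**Conclusion.** The point holds in a limited form. The stated adjustment uses control-period outcomes as both response and covariate, beside a random intercept that already carries the same information. It gained no precision in any reading tested.

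If the covariate spans the whole control period, a practice-only model has a standard error about 4-7% too small and a type I error of about 6-7%. With a GP random effect the excess is about 0.2-1.2 points. With a first-month baseline it is slight. Severity is minor to moderate.

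These sizes assume no true effect, no secular trend, 60 consultations in every practice-month and a truly exchangeable correlation. The patient level was not simulated, and the GP variance split is assumed.

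**What to change.** Remove the practice's control-period referral level from the adjustment set of every model that includes control-period consultations, and let the practice random intercept carry it. Keep the other GP-level and patient-level covariates. This is one line in the analysis plan and loses no precision.

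The alternative is to define baseline explicitly and exclude those months from the outcome data. That costs more. Planned control consultations number 3 x 60 x (1+2+3+4+5+6) = 3,780. Excluding the common first month removes 18 x 60 = 1,080 of them (29%) and leaves the three first-step practices with no control data. Excluding the whole control period would leave no control data at all. Dropping the covariate is the simpler choice.

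The planned interaction with baseline referring level is a separate question that this change does not settle.
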